**tDCS**

A battery operated tDCS device (SmartStim Model 1000; Nuraleve, Inc., Sudbury ON) with a maximum 4 mA capacity will be used to administer stimulation. tDCS will be applied by two cutaneous anodal and cathodal electrodes – 35cm^2^ and 100cm^2^, respectively. Each electrode will consist of conductive carbon enclosed in a saline-soaked sponge connected to lead wires attached to the tDCS device. An elasticized headband will hold the electrodes in place. The electrode configuration will be left anodal tDCS following the montage successfully demonstrated in a number of tDCS addiction studies (Boggio et al. 2009; Fregni et al. 2008a). The anode and cathode will be applied to the F3 and F4 regions, respectively, as defined by the standard International EEG 10-20 system (Jasper 1958). Stimulation will consist of 2 mA direct current delivered continuously for 20 min. This conforms to parameters of a recent 5-session study on cigarette craving (Boggio et al., 2009) and numerous other studies with clinical (depressed, substance dependent) and healthy participants (see Feil and Zangen, 2011 for review). Active treatment will consist of a current ramp up over 30 seconds to minimize discomfort, followed by 2mA stimulation over 19 minutes and subsequent ramp down over the final 30 seconds. Sham treatment will include a 30 second ramp up and 30 second ramp down at the beginning and end of the treatment session since tingling is commonly felt at the onset and termination.

**Pharmacological treatment**

Varenicline as per standard prescribing for dose escalation (i.e. Days 1 to 3: 0.5 mg once daily; Days 4 to 7: 0.5 mg twice daily; Days 8 to end of treatment: 1 mg twice daily) will be given concurrently over the same 2 weeks as the tDCS protocol and continue for an additional 10 weeks as per standard treatment duration recommended on the product monograph for a total of 12 weeks of varenicline treatment. Dose adjustments due to adverse events will be allowed (i.e. decrease to 0.5 mg twice daily).

The target quit date for smoking cessation will be on the last day of the two weeks of daily tDCS which corresponds to the recommended quit date after starting varenicline treatment. Subjects will return to the clinic every two weeks for a ‘booster session’ of tDCS. Their mood and smoking behaviour will be assessed and documented including any withdrawal or craving symptoms.

**Management of Adverse Events (AE) and Serious Adverse Events (SAE)**

Side Effects in a study examining the side effects of 567 sessions of tDCS (Poreisz et al. 2007) with 77 healthy controls and 25 patients, tDCS was associated with a mild tingling sensation (70.6%) as well as moderate fatigue (35.3%) and a light itching sensation under the stimulation electrodes (30.4%). After tDCS, a headache (11.8%), nausea (2.9%) and insomnia (0.98%). 21.6% of volunteers experienced a slight burning (1.59±0.91) and 15.7% experienced a mild pain sensation (1.41±0.71) under the electrodes during the stimulation. 17.7% of the volunteers experienced tDCS as mildly unpleasant. The most common side effects of varenicline are nausea, abnormal dreams, constipation, flatulence and vomiting in 30, 13, 8, 6 and 5% of users, respectively. They are reversible and usually not severe. It is not known whether combining the two treatments will increase either the incidence or the severity of adverse effects, especially those that are common between the two treatments such as nausea and headache.

If a participant experiences an adverse event that requires hospitalization or results in lasting harm or death (SAE) and can reasonably be attributed to tDCS stimulation, the trial will be immediately suspended. Adverse events that can be expected based on the known profile of tDCS side effects will be managed by the Qualified Investigator ([name]). Depending on the severity of the unexpected adverse event, the Qualified Investigator will decide if the trial should be suspended. All SAEs, AEs and UAEs will be reported to the CAMH Research Ethics Board. The emergency contact for reporting SAEs is the Qualified Investigator ([name]).

**Neuroimaging**

The fMRI neuroimaging component to this study will attempt to answer several research questions and address some of the gaps in the tDCS literature. Specifically, how does tDCS and/or varenicline alter functional connectivity between PFC and amygdala or insula? Does the magnitude of change predict successful cessation and long-term abstinence? Does active tDCS change the BOLD response to smoking cues and/or emotional cues? What is directionality of this effect?

Prior to MRI scans, participants will be required to complete a training session at least 24 hours prior to their first scan using the mock MRI scanner, a device which stimulates the scanner conditions including the screen-response apparatus. MRI tasks will be explained to participants outside the scanner and they will then be able to complete mock versions of the cue-reactivity and reward anticipation tasks. Participants who cannot appropriately complete the tasks or who demonstrate excessive motion or discomfort in the scanner due to the confined environment will be excluded from participation in the study.

Magnetic resonance imaging (MRI) will take place at the CAMH Research Imaging Centre (GE Discovery MR750 3T, General Electric Medical Systems, Milwaukee, WI) on 3 occasions: 1) at baseline following 12 hours of smoking abstinence (abstinence scan) 2) at baseline within 1 hour of smoking a cigarette (satiated scan) and 3) at end of the 12 week varenicline treatment. Baseline scans will occur within 1 week of each other and the order of satiated and abstinent scans will be counterbalanced to control for possible order effects. During each session, we will measure: 1) functional activation (blood-oxygen-level-dependent (BOLD) response) while subjects perform cue reactivity and reward anticipation task; resting state functional connectivity (rsFC) 3) quantitative T1 mapping (qMRI) and/or 4) Diffusion Tensor Imaging (DTI).

*Measures at rest*

The following measures (rsFC, DTI, qT1) will be collected with the subject at rest, i.e., no task performance will be required. qT1 images will be acquired across the whole brain. Diffusion Tensor Imaging (DTI)

DTI is a widely used MRI technique for measuring water diffusion within specific areas of the brain by quantifying the intensity of each image element, which in turn, reflects the rate of water diffusion. DTI is a useful measure for identifying white matter microstructures and has been shown to significantly alter brain tractography in adult smokers in areas such as the corpus callosum (Paul et al., 2008, Hudkins et al., 2012, Lin et al., 2012). DTI will be used to test for significantly tractography and/or white matter differences that may exist between active tDCS vs sham.

Resting state functional connectivity (rsFC)

rsFC is a task-independent measure of brain activity that is based on correlations between low frequency fluctuations of BOLD signal between brain regions in the absence of an explicit task (Biswal et al., 1995). Smoking has been shown to affect rsFC in the ventral and dorsal striatum, the insula and limbic systems (Ding et al., 2013, Janes et al., 2012, Sweitzer et al., 2016). rsFC data will be used to evaluate if there are differences in rsFC between active tDCS and sham and also if these rsFC networks are correlated with quit at end of treatment.

*Brain structure:* Structural MRI studies have identified cortical thickness, white matter, and volumetric abnormalities in smokers in cerebellum, striatum, cingulate cortex, prefrontal cortex, and insula using voxel-based morphometry (VBM) (see (Azizian et al, 2009) for review), and these, in turn, relate to cigarette exposure and craving (Morales et al, 2014). Quantitative T1-weighted MRI measures (qMRI) can shed additional light on the tissue microstructure underlying these findings, and allows for quantification (rather than only visualization) of results. These measures will be used to assess and detect subtle brain tissue alterations in both grey and white matter before and after tDCs treatment and/or smoking cessation. These neuroimaging parameters have never been assessed for changes resulting from abstinence from smoking nor have they been assessed in the context of tDCS treatment.

Each MRI scan will be preceded by an assessment of withdrawal, mood, and craving (Questionnaire of Smoking Urges (QSU; Tiffany & Drobes, 1991); POMS (Profile of Mood States)). Breathalyzer tests and urine samples will be collected at all scans to confirm abstinence from alcohol and other drugs of abuse prior to scans

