**METHODS**

**Design**

This will be a double-blind sham-controlled two-arm randomized clinical trial. Fifty participants will be randomized (1:1) to each arm. Arm 1 will be active tDCS plus varenicline (n=25) and Arm 2 will be sham tDCS plus varenicline (n=25). Treatment duration will be 12 weeks. Subjects will be required to attend an in person assessment visit. They will then be randomized to a condition. Neuroimaging scans (fMRI) and eye-tracking tests will be conducted in all participants at baseline. Participants will undergo two scans at baseline on different days within the same week: one in a satiated state and one in a non-satiated state. The same tasks will be performed at each scan. s. Following the baseline fMRI scans and eye-tracking tests, subjects will start taking the varenicline simultaneous with starting the tDCS regimen whereby they will come to the clinic every day (Monday to Friday) for the first 2 weeks to undergo the stimulation (active: 20 minutes at 2mA, sham: 30 seconds at 2mA and then nothing). Their target quit date will be at the end of this 2 week period. They will return to the clinic every two weeks for the next 10 weeks for a booster tDCS session and to complete questionnaires. Eye tracking tests will be conducted at the end of the fourth and eighth weeks. At the end of the 12-week treatment period they will undergo a third fMRI scan and eye-tracking tests. For the next 14 weeks they will be contacted weekly by e-mail or text message to report on their smoking status as measured by the 7 day point prevalence abstinence question. “Have you had a cigarette, even a puff, in the last 7 days?” At the 6-month time point subjects will be asked to return to the clinic for a brief visit to confirm smoking abstinence using expired CO and urinary cotinine and to complete questionnaires.

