**Participants**

Study participants will be 50 treatment seeking daily dependent smokers willing to make a quit attempt in the next 30 days. They will be recruited from our Nicotine Dependence Clinic and from the Greater Toronto Area through paid advertising in local newspapers and through the CAMH Registry and the CAMH website. Participants will have no concurrent Axis I psychiatric disorder (or history of substance use disorder), based on SCID, and be free of psychoactive drugs and medications, based on self-report and urinalysis. To ensure against subtle neurological deficits associated with sub-clinical alcohol misuse, men will be required to drink no more than 12 standard drinks per week and women will be required to drink no more than 9 drinks per week. These values conform to safe drinking limits for non-problem drinking (Sobell and Sobell, 1992). According to standard protocols for tDCS clinical trials, participants will also be excluded if they: a) have had recent clinically significant head trauma; b) have a history of seizures and/or epilepsy; c) are pregnant or planning to become pregnant; d) have pacemakers or implanted electrical devices such as cochlear implants; e) have metal embedded in the skull; or f) have skin lesions, open wounds, bruising, or similar injuries at either of the stimulation sites.

*Eligibility Criteria*

- Male or female
- Ages 19-65
- Daily smoker > 8 CPD
- Seeking treatment to quit smoking
- No current/recent DSM-IV Axis I diagnosis (apart from nicotine dependence)
- No current use of psychoactive drugs or medications
- No current use of Nicotine Replacement Therapy, e-cigarettes, or other medications for smoking cessation
- No history of seizures/epilepsy
- No metal embedded in the skull and/or implanted electrical devices
- No head injury (no concussion – diagnosed by a physician; OR no blow to the head with loss of consciousness for more than 1 hour)
- No known contraindications to fMRI
- No known contraindications to Varenicline
- Able to attend daily appointments for tDCS for the first 2 weeks and then once every 2 weeks for the next 10 weeks.
- Willing to undergo three fMRI scans – two at baseline and another at the end of treatment.

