**Outcome Measures**

The primary outcome measure will be continuous abstinence from smoking during weeks 9 – 12 as reported at clinic visits during those 4 weeks and confirmed using expired CO. Subjects will be classified as treatment responders if they respond “no” to the question: Have you smoked any cigarettes (even a puff) in the last seven days?

The key secondary outcome measures are:

1. Self-reported 7 day point prevalence abstinence throughout weeks 2 to 12 confirmed by expired CO at each clinic visit. To calculate survival curves we will also collect self-reported continuous abstinence weeks 9 through 26. For weeks 13 to 25, this will be collected via email or text message. For week 26, subjects will attend a brief clinic visit so abstinence can be confirmed with expired CO and urinary cotinine using a semi-quantitative dipstick. We hypothesize that the active tDCS group will have higher rates of abstinence (less relapse) than the sham tDCS group.

2. fMRI: change in Blood Oxygen Level Dependent (BOLD) activation in brain regions known to be associated with drug craving and emotion processing/regulation. MRS: GSH levels measured in a single voxel placed over prefrontal cortex. Fractional anisotropy (FA) values will be extracted from DTI analysis from regions of interest (ROIs) or to form probabilistic tractography for the whole brain. Network maps will be extracted and analyzed from the resting state functional connectivity measure.

3. Eye Tracking tests: changes in attentional bias to smoking-related cues and negative emotional cues. Attentional bias to high-arousal/high-risk cues.

*Self-Report Measures*

Participants will complete the 10-item Questionnaire of Smoking Urges-Brief (QSU-10; Tiffany and Drobes, 1991) and the Minnesota Nicotine Withdrawal Scale (MNSW; Toll et al, 2007) at each treatment session upon arrival and immediately after tDCS. They will complete a Side Effects Checklist ([name] et al., 1995) at the end of each treatment session.

Trait scales to be completed at baseline will include the FTND (Heatherton et al 1991) and Alcohol Use Disorders Identification Test (Saunders et al., 1993), 90-day Alcohol Timeline Followback (TLFB; Sobell and Sobell, 1992); 30-day Tobacco Timeline Followback (adapted from alcohol TLFB); Sensation Seeking Scale (Zuckerman et al., 1978).

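### Connectivity change cannot predict weeks 9–12 cessation, because it is first measurable at the end-of-week-12 scan, when that outcome is already determined

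*Protocol*

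**What the plan says.** The Neuroimaging section opens with questions about connectivity between prefrontal cortex and amygdala or insula, and then asks: "Does the magnitude of change predict successful cessation and long-term abstinence".

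Three scans are planned. Two are at baseline, within a week of each other; the other is placed "3) at end of the 12 week varenicline treatment". The Design section agrees ("At the end of the 12-week treatment period they will undergo a third fMRI scan and eye-tracking tests"), as does the eligibility list ("Willing to undergo three fMRI scans – two at baseline and another at the end of treatment"). No scan falls between the start of treatment and the end of week 12.

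Under Outcome Measures, cessation is "continuous abstinence from smoking during weeks 9 – 12 as reported at clinic visits", confirmed by expired CO. The Pharmacological treatment section sets the target quit date at the end of week 2.

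The resting-state subsection reports that smoking affects connectivity in the striatum, the insula and limbic systems. It plans to test "also if these rsFC networks are correlated with quit at end of treatment". Data Analysis expects baseline imaging to predict relapse.

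**The concern.** A predictor has to be measured before the outcome that it predicts. Here the change score is completed only when the cessation window closes. Participants who stopped smoking come to the third scan after at least four weeks without a cigarette, and possibly about ten if they stopped on the target quit date. If stopping smoking shifts connectivity, which the protocol's own background makes plausible, the two outcome groups will differ in change even if connectivity had no influence on who quit.

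At stake is what the imaging component can conclude. A measure obtained at week 12 cannot forecast or select who will be abstinent in weeks 9–12, and a consequence of quitting could be published as a neural marker of treatment success.

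**Working it through.** **1. Time order (no assumptions needed).**

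| Event | Time | Protocol section |
|---|---|---|
| Scans 1 and 2 | Baseline | Design; Neuroimaging |
| Target quit date | End of week 2 | Pharmacological treatment |
| Cessation window | Weeks 9–12 | Outcome Measures |
| Scan 3 | End of week 12 | Design; Neuroimaging |
| Weekly smoking reports | Weeks 13–25 | Outcome Measures |
| Confirmed clinic visit | Week 26 | Outcome Measures |

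Change = scan 3 minus baseline, so it exists only from the end of week 12. Its lead time over the weeks 9–12 outcome is zero at best. Its lead time over smoking in weeks 13–26 is positive. The baseline scans precede both outcomes.

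**2. Is the reverse direction plausible on the protocol's own terms?** Yes. The resting-state subsection says that smoking affects connectivity in the insula. The baseline scans are also deliberately split by smoking state (after 12 hours' abstinence, and within 1 hour of a cigarette), while no state is given for scan 3. One post-baseline scan cannot separate change that led to quitting from change that followed it.

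**3. The plan's own figure, and the risk set it implies.** The sample-size section sets 40% against 80% abstinence with 25 per arm. The usual two-proportion formula, two-sided 0.05 and 80% power, gives

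n = [1.96·√(2·0.6·0.4) + 0.84·√(0.4·0.6 + 0.8·0.2)]² / 0.4² = 22.3, so 23 per arm.

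Power at 25 per arm is 84.5% by the same method and 78.8% by Fisher's exact test, so the stated figure is reproduced closely. These rates give the number abstinent at week 12 if all 50 are scanned:
- 40% in both arms: 0.40 × 50 = 20
- 40% and 80%: 0.40 × 25 + 0.80 × 25 = 10 + 20 = 30

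**4. Illustration of how easily a consequence would show up.** Assume that change has no prior relation to quitting and that quitting itself shifts it by d standard deviations. The values of d are assumptions; the protocol gives none. With 20 quitters and 30 non-quitters, a two-sided t-test at 0.05 has 48 degrees of freedom and non-centrality d·√(20·30/50) = 3.46·d.

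| Assumed d | Non-centrality | Probability of p < 0.05 |
|---|---|---|
| 0.3 | 1.04 | 17% |
| 0.5 | 1.73 | 40% |
| 0.8 | 2.77 | 78% |

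A simulation with N = 50 and 40–60% quitters agrees: 38–39% at d = 0.5 and 76–79% at d = 0.8, with an apparent area under the ROC curve of about 0.64 and 0.71–0.72. A pure consequence of quitting can thus look like moderate discrimination.

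**The case against.** The strongest reply is that the quoted sentence is a research question rather than a specified analysis. Data Analysis contains no model that uses imaging change to predict weeks 9–12 abstinence. It compares imaging between groups and over time, relates it to craving, mood and withdrawal, and makes a validly ordered statement about baseline measures and relapse. The structural-imaging text openly allows that abstinence may cause brain change, and the background describes the imaging aim as exploring correlates. All of this is accurate and limits the weight of the point. It does not remove it: the question and the scan calendar are both fixed in the protocol, and no later analysis detail can put a week-12 change score before weeks 9–12.

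Four stronger readings are tempting and are not supported.

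- A reader might infer that the resting-state sentence has the same fault. It speaks only of correlation with quitting and does not mention change, so it can stand.
- A reader might infer that all non-quitters are smoking at scan 3. Under the even-a-puff rule, a single lapse in week 9 makes someone a non-quitter who may be abstinent by the scan, which would dilute the contrast.
- A reader might take the 40% to 78% above as an inflated false-positive rate. It is the power to detect an association assumed to be real; only the label of predictor would be wrong.
- A reader might infer that long-term abstinence is also settled before the scan. That is so only for the weeks 9–26 continuous measure in someone who has already smoked. Weekly point prevalence after week 12 and the confirmed week-26 visit follow the scan.

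**Conclusion.** The point holds for the successful-cessation half of the question. Change in connectivity cannot be a predictor of weeks 9–12 abstinence under this schedule, and a difference by quit status may be a result of quitting. This rests only on the scan dates and the outcome window; the 0.3–0.8 SD illustration is not needed for it and is not an error rate taken from the protocol. For relapse after week 12 the order is right, provided that the analysis starts at the scan. The question is secondary and exploratory in a 50-person pilot. The primary abstinence comparison, the randomised imaging comparisons and prediction from baseline scans are unaffected. The change is still worth making, because it determines what the imaging component may claim.

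**What to change.** Reword the question in the Neuroimaging section as three parts; the resting-state sentence needs no change.

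- (a) To predict weeks 9–12 abstinence, use the two baseline scans only.
- (b) Use baseline-to-week-12 change as a predictor only for relapse in weeks 13–26, among participants abstinent at the third scan, with time counted from that scan and treatment arm in the model. Do not use the weeks 9–26 continuous measure for this, since it begins before the scan.
- (c) Describe any link between change and weeks 9–12 status as an association.

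This adds no scans, visits or participants. The cost is precision in (b): about 20 to 30 people under the sample-size section's rates, fewer if scans are missed, so its results should be presented as estimates with wide intervals.

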**Cognitive Tasks**

*Cue reactivity paradigm*

In this task, subjects are presented with a series of smoking-related and neutral photographic cues, adopted from the International Smoking Image Series (Gilbert et al, 1999). Smoking cues include photographs of people smoking and smoking-related objects such as packs of cigarettes and ashtrays. Neutral cues consist of neutral themed pictures selected not to elicit strong emotional responses, such as neutral faces, flowers, or furniture. Visual cues will be presented in a block design, with 4 pictures/block, lasting a total of 20s (5s/picture). There will be 8 blocks of neutral and smoking cues each, presented in a random order, and all pictures presented within each block will be randomized. Each picture block will be interspersed with a rest fixation cross block lasting 18s.

*Monetary Reward Anticipation Task Paradigm*

This task was designed by Garrison et al. (Garrison et al., 2017), which was modified version of the MIDF from Knuston et al. (Knuston et al., 2000). This task was designed based on evidence that drugs of addiction, such as nicotine, alters brain sensitivity in regions specifically involved in motivation and reward (Robinson et al., 2001). Specifically, chronic drug use is associated with responsibility to drug related cues in the mesocorticolimbic dopaminergic reward circuit in the ventral striatum and medial prefrontal cortex (Koob et al., 2010). Thus, impairment in reward processing in addiction could contribute to the drug seeking behaviour and decrease treatment effectiveness. Participants are primed for 6 seconds with possible shapes representing condition cue-indicators, which indicate the possibility of monetary gain, monetary loss, verbal feedback (procedural control), or request no response (control). Immediately following the cue image presentation, a prespecified stimulus will prompt participants to respond as quickly as possible to either: receive a reward, prevent reward loss or receive feedback on their performance. The reaction time required for a registered response is adapted on a trial-by-trial basis such that all participants will receive similar earnings by the end of the task. Participants will practice the task prior to scans to minimize learning effects. The participants will receive a maximum of $20 for each time they do this task.

